## **2.3 THE NEED FOR THE TRIGGER TRIAL**

This trial is designed to use the mrTRG as a biomarker for response. No prospective trials have stratified rectal cancer management according to the mrTRG or any other biomarker for response to treatment. Initially the feasibility study will assess ability to recruit patients and to deliver mrTRG directed management. If this is successful we intend to perform a phase III trial that will assess whether mrTRG can improve quality of life and overall survival through a personalised MRI directed dual management approach; 'poor responders' will be offered additional treatment to enable further downstaging and early treatment of systemic relapse risk and 'good responders' will be offered deferral of surgery, potentially avoiding the morbidity and mortality of surgery.

## **3. TRIAL DESIGN**

### **3.1 TRIAL OVERVIEW**

This is a feasibility study intended to establish safety and feasibility of recruitment numbers for the larger phase III study. The feasibility protocol will continue as a phase III study subject to the two conditions of feasibility being met i.e. (1) reaching target recruitment rates of 6/mth during the last 4 months of recruitment and (2) Funding is received for the main Phase III trial. At this point a substantial amendment will be submitted to include the primary endpoint for the Phase III trial of disease-free survival from the point of registration. Recruitment to feasibility will continue until the Phase III component is approved to enable the TMG to report on the secondary endpoints of the feasibility component of the trial. Data from patients in the feasibility study will be included in the final analysis of the phase III study. This is intended to optimize recruitment. It is subject to the trial safety standards and stopping rule. The Royal Marsden will remain as trial sponsor for the duration of the feasibility and Phase III studies.

This is a multicentre, prospective, open, randomised control trial. It is not possible to blind the patient, radiologist, surgeon or pathologist but prospective proforma based reporting by the radiologists and pathologists will increase the objectivity of data recorded.

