### 4.4 TRIAL ENDPOINTS

#### 4.4.1 PRIMARY ENDPOINT

The total number of patients randomised per month during the last 4 months of recruitment.

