#### **14.1.2 FEASIBILITY STUDY SAMPLE SIZE**

In this feasibility study a type II error would result in the cancellation of the planned phase III study when the recruitment rate was in fact sufficient to support such a study. We wish to minimise the probability of this occurring and so have set the chance of a type II error (B) at 5% and the resulting power (1-B) at 95%. A type I error would result in the planned phase III study going ahead when the true recruitment rate is poor. We would accept a 10% chance of this occurring and so have set the significance threshold (alpha) at 0.1.

The sample size for the primary endpoint of the feasibility study can be worked out as follows:

Recruitment of at least 633 patients to the phase III trial is planned to take place over a total of 3 years, and should take at most no more than 5 years. Hence the recruitment rate is expected to be 11 patients per month and will need to be no less than 5-6 patients per month (5/month results in total time of 6.5 years,

6/month results in 5.5 years total). In a similar multicentre trial sponsored by RM (6 vs. 12), recruitment rates over time were as follows:

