**Table: Recruitment rate in previous multi-centre trial (6 vs. 12)**

| Date of TMG   | N centres open | Rate per month from last TMG to current | Rate per month per centre |
|---------------|----------------|-----------------------------------------|---------------------------|
| Sept 2011     | 8              | 2                                       | 0.3                       |
| Dec 2011      | 9              | 6                                       | 0.7                       |
| March 2012    | 10             | 7.7                                     | 0.8                       |
| July 2012     | 12             | 7.3                                     | 0.6                       |
| December 2012 | 15             | 4.6                                     | 0.3                       |

In order to calculate the required sample size, we ran a simulation in which a set of observations from a Poisson distribution with mean 11 were generated. A Chi-squared goodness of fit test of the null hypothesis that these observations were from a Poisson distribution with mean 6 was performed, and rejected if the resulting p-value was equal or less than 0.1. Using a total of 4 observations resulted in power between 95 and 96% with 10,000 replicates. In order to allow enough time for sites to open and collect sufficient data to allow a preliminary assessment of the safety of the deferral of surgery approach and the safety and acceptability of additional pre-operative chemotherapy, the maximum feasibility recruitment period will be 24 months. The primary hypothesis will be tested based on the average rate of recruitment in the four months following the activation of the 12th participating site, or the average rate of recruitment in the final four months of the feasibility recruitment period, whichever is earlier.

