## 14. 2 ANALYSIS METHODS

### 14.2.1 PRIMARY ENDPOINT

The primary endpoint of this study is the total numbers of patients randomised per month, during the last 4 months of recruitment. A chi-squared goodness of fit test with one-sided alpha of 0.1 will be used to test the null hypothesis that the expected number of patient recruitment per month is equal to 6. Rejection of the null hypothesis would suggest that recruitment levels are adequate to support the proposed phase III study with sample size and length of recruitment as described in this protocol. However if the null hypothesis is not rejected then exact recruitment rates by time for each centre will be stated, and any known reasons for low recruitment investigated. After taking these results into consideration it may still be deemed possible to proceed with a phase III study if the design is amended accordingly. The primary endpoint for the feasibility study will be stated in full in the phase III protocol before seeking final approval.

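### Section 3.1 opens phase III when recruitment reaches 6 per month, the rate that sections 14.1.2 and 14.2.1 set out to reject, and the four-month window is defined in two ways

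*Protocol*

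**What the plan says.** **Progression rule in 3.1.** The feasibility protocol continues as a phase III study if two conditions are met. The first is "reaching target recruitment rates of 6/mth during the last 4 months of recruitment". The second is that "Funding is received for the main Phase III trial". A substantial amendment follows. Section 3.1 adds: "Recruitment to feasibility will continue until the Phase III component is approved to enable the TMG to report on the secondary endpoints".

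**Error rates in 14.1.2.** The false-positive decision is described as follows: "A type I error would result in the planned phase III study going ahead when the true recruitment rate is poor". The type II error is set at 5%. On the tolerance for the false-positive decision, the section says: "We would accept a 10% chance of this occurring and so have set the significance threshold (alpha) at 0.1". The expected rate is 11 per month and the floor is 5 to 6 per month. Power of 95 to 96% is reported for a chi-squared goodness-of-fit test on four Poisson observations with true mean 11 and null mean 6, rejecting at p of 0.1 or less.

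**Test in 14.2.1.** A chi-squared goodness-of-fit test with one-sided alpha of 0.1 is used to "test the null hypothesis that the expected number of patient recruitment per month is equal to 6". Rejection would suggest that recruitment is adequate for phase III with the sample size and duration described. Without rejection, centre-level rates are examined and phase III may still proceed if its design is amended.

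**Window.** Section 4.4.1 gives "The total number of patients randomised per month during the last 4 months of recruitment", and 3.1 and 14.2.1 also use the last four months of recruitment. Section 14.1.2 instead tests the average rate in the four months after the 12th site is activated, "or the average rate of recruitment in the final four months of the feasibility recruitment period, whichever is earlier", and caps feasibility recruitment at 24 months.

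**The concern.** One number has two opposite roles. In 3.1 a rate of 6 per month is a target, and an observed average equal to it is enough. In section 14 it is the rate that must be shown to be exceeded. A four-month average at or modestly above 6 meets the first and will usually not meet the second. By 3.1 the protocol then continues as phase III. By 14.2.1 the same data call for a review of centre rates and an amended phase III design.

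The window adds a second ambiguity. If the 12th site opens early, the 14.1.2 window and the last four months of recruitment are different months. Because 3.1 keeps recruitment open until phase III is approved, its last four months have no clear end when the progression decision has to be made.

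This is the trial's only primary endpoint and the gate to phase III. If 3.1 is the operative rule, the 10% risk chosen in 14.1.2 does not govern the decision.

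**Working it through.** **Inputs.** From 14.1.2 and 14.2.1: null rate 6 per month, planned rate 11 per month, four monthly counts, alpha 0.1. From 3.1: condition met at 6 per month over four months. Assumptions: monthly counts are independent Poisson, as in the protocol's own simulation, and reaching 6 per month means an average over the four months, which is how 14.1.2 describes the rate. The condition is then a total X of at least 4 × 6 = 24.

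**1. The protocol's stated power.** Take T = Σ(xᵢ − 6)²/6 over four months and reject if T is at least the 0.90 quantile of chi-squared.

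- With 3 df (critical value 6.25), the rejection probability at 11 per month is 95.8%, inside the stated 95 to 96%.
- With 4 df it is 93.0%.
- A 1-df chi-squared test on the total against 24 gives 96.4%.

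The 3-df version is therefore taken as the test that was simulated.

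**2. The recruitment condition in 3.1.** X is Poisson with mean 4 × the monthly rate.

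| True rate per month | Mean of X | P(X ≥ 24) |
|---|---|---|
| 5 | 20 | 0.213 |
| 5.5 | 22 | 0.363 |
| 6 | 24 | 0.527 |
| 11 | 44 | 0.9996 |

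If the total must strictly exceed 24, the probability at 6 per month is 44.6%.

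**3. Disagreement between 3.1 and the 3-df test.** P(X ≥ 24 and T < 6.25) is about 0.40 at a true 6 per month and 0.51 at 7 per month. Two examples show that the test does not follow the total:

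- Counts 9, 9, 9, 9 (total 36): T = 4 × 9/6 = 6.0, p = 0.11, not rejected.
- Counts 12, 4, 4, 4 (total 24): T = (36 + 4 + 4 + 4)/6 = 8.0, p = 0.046, rejected.

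**4. Whether pointing 3.1 at the test is enough.** The 3-df test has no direction. At a true 6 per month it rejects 17.5% of the time (11.4% with a mean above 6). At 3 per month it rejects 69% of the time, almost always because recruitment is low. So it does not deliver a one-sided 10% either.

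**5. A test that does.** For an exact one-sided Poisson test on the total, find the smallest c with P(X ≥ c | mean 24) ≤ 0.10.

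- c = 30: 0.132
- c = 31: 0.096

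The cut is 31 patients in four months (31/4 = 7.75 per month), with type I error 9.6% and power P(X ≥ 31 | mean 44) = 98.3%.

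**The case against.** - **Section 14.2.1 is not a veto.** A reader might infer that the same data give go in one section and no-go in another. The text does not say that: after non-rejection, phase III may still proceed with an amended design. The conflict is narrower. Section 3.1 continues to phase III at 6 per month without that review or that amendment.
- **A cut of 31 patients is not in the protocol.** It would be tempting to say that totals of 24 to 30 meet 3.1 and fail 14.2.1. No count is stated, and under the 3-df test a total of 24 can reject while a total of 36 does not. The disagreement is therefore measured above with the 3-df test; 31 belongs only to the proposed remedy.
- **The 53% needs its limits.** It covers the recruitment condition alone, before funding, at exactly 6 per month. Any threshold on an observed rate is passed about half the time at its own boundary, and 14.1.2 puts the floor at 5 to 6. That is fair, but 14.1.2 makes 6 the null and accepts a 10% risk of going ahead at a poor rate. At 5 per month the figure is still 21%.
- **Another reading of 3.1.** If every one of the four months had to reach 6, the condition would be met 9.4% of the time at 6 per month (85.8% at 11). Nothing in the text states that rule.
- **The window cannot be chosen freely.** A reader might infer that the more favourable period could be picked after the counts are seen. No section permits this; 14.1.2 gives a deterministic rule and a 24-month maximum. The difference in wording between 14.1.2 and the other three sections stands, as does the open end in 3.1.

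**Conclusion.** The progression rule is inconsistent as written and must be reconciled. Section 3.1 treats as sufficient the rate that section 14 sets out to reject. On a four-month-average reading with Poisson counts, the recruitment condition in 3.1 is met with probability 53% at a true 6 per month and 21% at 5 per month, against the 10% accepted in 14.1.2. With the 3-df test that matches the stated power, 3.1 is met without rejection about 40% of the time at 6 per month and 51% at 7 per month. The window has two definitions, and under 3.1 its end is unclear at the time of decision.

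The documents do not support calling this a 53% chance that phase III starts wrongly, or treating 14.2.1 as a strict stop. The defect lies in the feasibility gate; no comparison between the randomised arms depends on it.

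**What to change.** 1. In 3.1, replace condition (1) with rejection of the 14.2.1 null hypothesis, and refer there to the amended-design route that 14.2.1 allows after non-rejection.
2. In 14.2.1, specify a one-sided exact Poisson test on the four-month total at alpha 0.1, rejecting at 31 or more patients (type I error 9.6%). In 14.1.2, replace the simulated power with 98.3% at 11 per month. Without this change of test, linking 3.1 to 14.2.1 would not deliver the 10%.
3. Use the 14.1.2 window as the single definition in 3.1, 4.4.1 and 14.2.1. Keep the fallback to the final four months of the feasibility period, which may well be needed because 5.1 anticipates 10 to 15 sites.
4. State that patients randomised after that window do not enter the primary endpoint. Recruitment can then continue for the secondary endpoints as 3.1 intends.

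The cost is an amendment to four sections, including a change of test and a restated power. Recruitment and patient pathways are untouched. The sponsor should note that at a true 7 per month the 31-patient cut is reached only about 31% of the time (Poisson mean 28), so the amended-design route would be used often at intermediate rates.

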## **4.2 SECONDARY OBJECTIVES OF THE FEASIBILITY TRIAL**

### **1. Assess response rate by comparing the reported mrTRG in the control and intervention arm**

Trial participants are randomised with stratification for the key factors that effect response (tumour height, mrEMVI and chemotherapy). Therefore the mrTRG should be similar in the control and intervention arm. In order to avoid the MDT being informed of the mrTRG in the control arm we will report the mrTRG grade in the control arm by centralised assessment. Comparison between the mrTRG in the control versus intervention arm will allow us to evaluate the amount of additional response achieved by using 'upfront' systemic chemotherapy.

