### **2. Evaluate the reproducibility of mrTRG by assessing the strength of the agreement between the recruiting radiologists and central radiologist**

A prerequisite to opening a site is that the allocated radiologist is able to perform MRIs according to the published protocol and achieve a high Kappa agreement ( $k \geq 0.7$ ) with a training dataset that includes mrTRG grades and radiological evidence of regrowth. The central MRI review will also be used to identify any missed 'radiological regrowths' using the MRI training dataset. The agreement between the recruiting radiologists and central radiologist scored mrTRG grades for scans acquired during the study for patients randomised to the intervention arm will also be assessed retrospectively at the end of the feasibility trial.

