#### **7.4.1 ACTING ON THE RANDOMISATION**

The post-treatment MRI forms are different for the control and intervention arms of the trial – named **CONTROL ARM POST-TREATMENT MRI Form** and **INTERVENTION ARM POST-TREATMENT MRI Form** for the control and intervention arm respectively. Therefore it is crucial that the research team at each site inform the radiologist which arm the patient is in. We recommend that this is done by adding the allocated arm of randomisation and which POST-TREATMENT MRI Form to use to the radiology request card. As this is an open label study, the randomisation outcome should also be recorded in the patient's medical records.

The **CONTROL ARM POST-TREATMENT MRI Form** for the control arm does not include the mrTRG classification. Without this information, treatment should be planned according to current guidelines i.e. only the information from the baseline MRI should be used. If the patient is randomised to the intervention arm, mrTRG directed management should take place.

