## APPENDIX 5: HISTOPATHOLOGY

### HISTOPATHOLOGICAL EVALUATION OF THE RESECTION SPECIMEN

All pathology specimens will be prepared for evaluation in a standardized way, previously reported for the MERCURY and CR07 trials. Photographs of the specimens will be collected for central review of the quality of surgery and of the histology – to ensure these photographs are taken it is helpful to pre-warn the pathology department about the date of surgery and clearly mark the request form as being a TRIGGER trial case.

A full set of H and E stained glass slides and specimen photographs will be centrally reviewed and digitised at the Department of Pathology & Tumour Biology, Leeds Institute of Cancer and Pathology, University of Leeds, UK, the digitized pathology sections will then be archived on the BRC imaging and genomic profiling corelab library server. Central review at Leeds will ensure quality control – quality of surgery and analysis of potential response biomarkers such as ki67, tumour cell density. Centres will first send these slides to the Royal Marsden as detailed in the Laboratory Manual and can either send the original H&E stained glass slides or a set of copies.

All pathology data is routinely collected as part of the Royal College of Pathologists Reporting proforma, with the exception of effect of chemotherapy and radiotherapy on the tumour. This assessment of tumour regression is an important secondary outcome for The TRIGGER trial and mrTRG will be compared with Pathology assessment of tumour regression. Therefore the modified Mandard scoring assessment for chemo-radiotherapy response will be used.

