## Preparation of the specimen

The surgeon will be asked to provide information regarding the height of the tumour and its location within the bowel wall on the histopathology request form. This will help the pathologist to identify the tumour and is particularly important in cases showing an excellent response to pre-operative therapy.

The intact specimen should be photographed whole prior to opening the bowel and further dissection. It is preferable for the specimen to be submitted fresh from the operating room to the pathology department as soon as possible after resection. Upon receipt in the pathology department, digital colour photographs should be taken of the anterior and posterior surface of the whole specimen, preferably prior to formalin fixation (see example below). It may be advisable to ask the surgeon to take photographs of the fresh specimen following resection if this opportunity is likely to be missed in the pathology laboratory. All photographs **must** include a metric ruler (for calibration) and the site of the tumour and the high vascular

ties should be marked (e.g. with forceps or pre-printed labels). If the tumour location cannot be ascertained by palpation, this should be indicated on the photograph with an additional label. Additional images of the lateral views (left and right side), close ups of the anterior and posterior surfaces of the levator/sphincters (in abdominoperineal excision specimens), close ups of any perforation site or other defects, and any other unusual findings should also be taken.

[figure not shown]

The plane of surgery should be assessed by the local pathologist on the intact specimen (prior to opening) for both the mesorectum and the levator/sphincters (as appropriate). This is preferably done on the fresh specimen prior to fixation. If the specimen is received already fixed in formalin, grading and photography can be done at this stage prior to opening the specimen. Surgeons should be asked not to open specimens prior to receipt in the pathology department as this can affect the assessment of the surgical planes and the status of the CRM. The grading systems for the planes of surgery are given below.

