## TRANSFER

Please refer to the image transfer section of the Imaging Manual for details relating to scan anonymisation and transfer to the TRIGGER Trial Office. These scans will be stored electronically and the central review team at the Royal Marsden will review the scans retrospectively in batches and copies of the analytic data will be kept in the TRIGGER Trial Office at the Royal Marsden. **It is important to note that the local MRI reports, including mrTRG reported for those in the intervention arm, will be used by the site study team to guide patient management, not the central review.**

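### Section 3.1 says no radiologist or pathologist can be blinded, but the planned central reads could be masked to the site result and to arm, and the protocol does not require it

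*Protocol*

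**What the plan says.** - **Blinding.** Protocol section 3.1 describes an open trial and says: "It is not possible to blind the patient, radiologist, surgeon or pathologist". It makes no distinction between site and central readers. The only mitigation is that "prospective proforma based reporting by the radiologists and pathologists will increase the objectivity of data recorded".
- **Site radiologist.** Section 7.4.1 says "it is crucial that the research team at each site inform the radiologist which arm the patient is in", because the post-treatment MRI form differs by arm.
- **Between-arm mrTRG.** Section 4.2, objective 1, compares mrTRG between arms. To keep the grade from the control-arm MDT, "we will report the mrTRG grade in the control arm by centralised assessment". In the intervention arm the site radiologist reports it (sections 3.3 and 8.2).
- **Agreement.** Section 4.2, objective 2, and section 14.2.2 plan a site-versus-central mrTRG agreement analysis when the feasibility stage closes, restricted to one arm: "scans acquired during the study for patients randomised to the intervention arm will also be assessed retrospectively". Separately, a kappa of at least 0.7 on a training dataset is needed before a site opens.
- **Central MRI review.** Under image transfer in Appendix 6, "the central review team at the Royal Marsden will review the scans retrospectively in batches". The local report, not the central one, guides management.
- **Pathology.** Appendix 5 says "The plane of surgery should be assessed by the local pathologist on the intact specimen". It also says "Photographs of the specimens will be collected for central review of the quality of surgery", and describes the central review as quality control. Photographs and slides are labelled with trial ID, site code, initials and patient number. The local histopathology report is sent with the slides.
- **Analysis.** Sections 4.4.2 and 14.2.2 compare quality of surgery between arms, with a Mann-Whitney test. Section 14.2.2 also summarises endpoints within arm by mrTRG 1-2 versus 3-5.

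**The concern.** Site staff cannot practicably be masked in this design. Central readers can, and the protocol already pays for their reads. Because section 3.1 treats all readers alike, nothing tells the central team to read without the arm, the site mrTRG or the local plane grade.

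The consequences differ by endpoint. A second reader who has seen the first grade is not testing reproducibility, so the agreement statistic can be too high. A comparison between arms in which the two arms are graded by different readers, one of them unblinded, confuses reader with arm. A judgemental plane grade given by someone who may know the arm can move in either direction. All three results are meant to inform the phase III design, and section 3.1 says that feasibility patients will enter the phase III analysis.

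**Working it through.** No figure in the protocol depends on this point, so the check is a comparison of sections plus one illustration.

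**1. Which readers can be masked**

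| Reader | Must know the arm? | Read guides care? | Masking stated? |
|---|---|---|---|
| Site radiologist | Yes (7.4.1) | Yes (Appendix 6) | No; not feasible |
| Central radiologist | No reason given | No (Appendix 6) | None |
| Local pathologist | Not required, but the trial is open | Yes | None |
| Central pathologist | No; arm not among the listed labels (Appendix 5) | Described as quality control | None; local report comes with the slides |

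The section 3.1 statement therefore fits the first row. It does not fit the two central rows.

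**2. mrTRG agreement on trial scans**

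Only intervention-arm scans enter this endpoint. With 90 patients randomised 2:1, that is about 90 × 2/3 = 60 patients. There is no contrast between arms in this kappa, so the masking that matters is to the site grade.

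Kappa is k = (po − pe)/(1 − pe), where po is observed and pe is chance agreement. If the central reader adopts the site grade in a fraction a of the discordant pairs, po becomes po + a(1 − po). With pe taken as unchanged, kappa becomes k + a(1 − k).

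Take k = 0.60 as an assumption; neither it nor the values of a come from the protocol:

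- a = 0: 0.60
- a = 0.25: 0.60 + 0.25 × 0.40 = 0.70
- a = 0.50: 0.60 + 0.50 × 0.40 = 0.80

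**3. Between-arm mrTRG comparison**

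Control grades come from the central read and intervention grades are reported by unblinded sites. A central read of intervention scans is planned for the agreement endpoint, but no section says that it supplies the grade for this comparison, or that both arms are read together under masking. The same split affects the mrTRG 1-2 and 3-5 subgroups of section 14.2.2: control patients can be placed only by the central read.

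A common masked read is feasible for the post-CRT scan. Section 3.3 gives it the same timing in both arms (4-6 weeks, at most 10), before treatment diverges. Later intervention-arm scans have no control counterpart and cannot be masked to arm in this way.

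**4. Quality of surgery**

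Appendix 5 grades the mesorectal plane on three levels, and the levator/sphincter plane separately in APE specimens. The local pathologist assigns the grade. The protocol does not say whether the local or the central grade enters the Mann-Whitney test. On either reading, no masking is stated.

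**The case against.** The strongest reply is that section 3.1 speaks of the people who complete the proformas, that is the site readers, and that central procedures may be set out in the Imaging Manual, the Laboratory Manual or the statistical analysis plan, none of which is at hand. No section says that the central radiologist is shown the arm or the site mrTRG. That stands as a limit: masking may be described elsewhere. It does not remove the point, because the protocol's own sentence is unqualified and Appendix 5 does send the local report with the slides.

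Several stronger readings are tempting, and the documents do not support them:

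- *That these endpoints are biased.* The protocol shows that nothing prevents bias, not that it occurred.
- *That masking to arm would protect the agreement kappa.* It would not, since only intervention-arm scans are used.
- *That an inflated kappa would pass the protocol's standard.* The 0.7 is a site-opening threshold on a training dataset. No pass mark is set for trial scans.
- *That central readers should receive only the baseline and post-CRT scans.* The agreement endpoint covers scans acquired during the study, and intervention patients also have mid-chemotherapy, post-consolidation and surveillance MRIs. Such a rule would narrow the endpoint.
- *That a central grade should replace the local plane grade.* Appendix 5 prefers assessment on the intact, fresh specimen, with confirmation on slices. A grade from photographs gains masking but may lose validity.

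It is also fair that section 14.2.2 makes the secondary analyses descriptive, with exploratory tests, and that the decision to continue rests on recruitment and funding.

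**Conclusion.** The point holds in a limited form. The section 3.1 statement is too broad, and the protocol leaves three secondary results open to assessor influence that its own central reads could reduce: mrTRG agreement (through sight of the site grade), the between-arm mrTRG comparison and subgroups (through different, partly unblinded readers), and quality of surgery (through local grading in an open trial).

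The size cannot be derived from the documents. The kappa values of 0.70 to 0.80 rest on an assumed independent kappa of 0.60, assumed adoption of a quarter to a half of the discordant grades, and unchanged chance agreement. No direction or size can be given for the other two results. The primary endpoint is not touched. The change is worth making because it is cheap and because these results feed phase III.

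**What to change.** 1. In section 3.1, limit the statement on blinding to patients, treating clinicians and site readers.
2. In Appendix 6, require central MRI reads to be masked to the site mrTRG for every scan in the agreement endpoint.
3. For the post-CRT scan, read both arms in mixed batches masked to arm. Use that central read for the between-arm mrTRG comparison and for the mrTRG subgroups in both arms.
4. In Appendix 5, require central pathology review to be masked to arm and to the local plane grade. Report the quality-of-surgery comparison with the masked central grade alongside the local grade.
5. Withhold local forms and reports from the central reader only, until the central grade is entered. CRF return within one month (section 12.5) and expedited reporting of pCRM involvement to the Trial Office (Appendix 1, section 2.1.4) then stay as they are.

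The reads themselves are already planned. The cost is a withholding step at the Trial Office and the laboratory. Masking will be incomplete in some cases, and some central plane grades will be missing where photographs are inadequate.
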